### Follow-up time and study discontinuation all arms - Full Analysis set\* (N=40)

|                                           | Etoricoxib
(N = 10) | H56:IC31
(N = 12) | Controls
(N = 10) | Etoricoxib +
H56:IC31
(N = 8) |
|-------------------------------------------|------------------------|----------------------|----------------------|-------------------------------------|
| Follow-up time in days             |                        |                      |                      |                                     |
| Mean (SD)                                 | 242.7 (12.7)           | 227.3 (44.4)         | 246.7 (39.0)         | 241.4 (36.6)                        |
| Min, Max                                  | 220.0, 265.0           | 88.0, 250.0          | 168.0, 330.0         | 180.0, 285.0                        |
| Did the subject complete the study |                        |                      |                      |                                     |
| Yes                                       | 9 (90%)                | 10 (83%)             | 9 (90%)              | 6 (75%)                             |
| No                                        | 1 (10%)                | 2 (17%)              | 1 (10%)              | 2 (25%)                             |
| Reasons for study discontinuation  |                        |                      |                      |                                     |
| Voluntary discontinuation by the subject  | 0 (0%)                 | 1 (50%)              | 0 (0%)               | 0 (0%)                              |
| Pregnancy during follow-up                | 0 (0%)                 | 0 (0%)               | 1 (100%)             | 1 (50%)                             |
| Moved abroad                              | 1 (100%)               | 1 (50%)              | 0 (0%)               | 1 (50%)                             |

\*Full analysis set (FAS) defined as randomized patients with at least one valid immunogenicity measurement

**Adherence to Etoricoxib - Safety Analysis Set\* (N=13).**

|                                                                               | Total
(N = 13)  |
|-------------------------------------------------------------------------------|--------------------|
| Proportion of tablets taken from the number expected                   |                    |
| Mean (SD)                                                                     | 96.0 (8.8)         |
| Median (Q1, Q3)                                                               | 99.3 (98.7, 100.0) |
| Min, Max                                                                      | 73.5, 102.9        |
| Proportion of tablets taken from the number expected in two categories |                    |
| <80% of expected tablets                                                      | 2 (15%)            |
| ≥80% of expected tablets                                                      | 11 (85%)           |

**Adherence to H56:IC31 - Safety Analysis Set\* (N=12)**

|                                 | Total
(N = 12) |
|---------------------------------|-------------------|
| First vaccination given  |                   |
| No                              | 1 (8%)            |
| Yes                             | 11 (92%)          |
| Second vaccination given |                   |
| No                              | 2 (17%)           |
| Yes                             | 10 (83%)          |

**Adherence to Etoricoxib + H56:IC31 - Safety Analysis Set\* (N=10)**

|                                                                               | Total
(N = 10)   |
|-------------------------------------------------------------------------------|---------------------|
| Proportion of tablets taken from the number expected                   |                     |
| Mean (SD)                                                                     | 98.3 (2.5)          |
| Median (Q1, Q3)                                                               | 100.0 (96.4, 100.0) |
| Min, Max                                                                      | 92.8, 100.0         |
| First vaccination given                                                |                     |
| No                                                                            | 2 (20%)             |
| Yes                                                                           | 8 (80%)             |
| Second vaccination given                                               |                     |
| No                                                                            | 2 (20%)             |
| Yes                                                                           | 8 (80%)             |
| Proportion of tablets taken from the number expected in two categories |                     |
| ≥80% of expected tablets                                                      | 10 (100%)           |

\*Safety analysis set defined as patients that received at least one dose of etoricoxib and/or one dose of H56:IC31

**Adherence to Etoricoxib - Full Analysis Set\* (N=10)**

|                                                                               | Total
(N = 10)  |
|-------------------------------------------------------------------------------|--------------------|
| Proportion of tablets taken from the number expected                   |                    |
| Mean (SD)                                                                     | 96.9 (8.4)         |
| Median (Q1, Q3)                                                               | 99.6 (99.3, 100.0) |
| Min, Max                                                                      | 73.5, 102.9        |
| Proportion of tablets taken from the number expected in two categories |                    |
| <80% of expected tablets                                                      | 1 (10%)            |
| ≥80% of expected tablets                                                      | 9 (90%)            |

**Adherence to H56:IC31 - Full Analysis Set\* (N=12)**

|                                 | Total
(N = 12) |
|---------------------------------|-------------------|
| First vaccination given  |                   |
| No                              | 1 (8%)            |
| Yes                             | 11 (92%)          |
| Second vaccination given |                   |
| No                              | 2 (17%)           |
| Yes                             | 10 (83%)          |

# Adherence to Etoricoxib + H56:IC31 - Full Analysis Set\* (N=8)

|                                                                               | Total
(N = 8)   |
|-------------------------------------------------------------------------------|--------------------|
| Proportion of tablets taken from the number expected                   |                    |
| Mean (SD)                                                                     | 97.9 (2.7)         |
| Median (Q1, Q3)                                                               | 98.9 (96.1, 100.0) |
| Min, Max                                                                      | 92.8, 100.0        |
| First vaccination given                                                |                    |
| Yes                                                                           | 8 (100%)           |
| Second vaccination given                                               |                    |
| Yes                                                                           | 8 (100%)           |
| Proportion of tablets taken from the number expected in two categories |                    |
| ≥80% of expected tablets                                                      | 8 (100%)           |

\*Full analysis set (FAS) defined as randomized patients with at least one valid immunogenicity measurement. To acknowledge the possible impact of poor compliance to allocated treatment on immunogenicity, we defined compliance for each group based on a priori definitions. A participant was considered compliant if no corticosteroids/additional NSAIDs during the last seven days prior to sampling were taken. If allocated to etoricoxib, ≥80% of prescribed daily doses had to be taken during 1) the day 0-140 interval, and 2) the last 7 days prior to sampling. If allocated to H56:IC31-vaccine, ≥1 H56:IC31-vaccine were administered.

**Supplementary Table 9. Adverse events (AE) tables Day 0 to day 84. Safety Analysis Set\* (N=47)**

**Summary of AEs**

|                                                    | etoricoxib N=13 | H56:IC31 TB vaccine N=12 | Control N=12 | etoricoxib and H56:IC31 TB vaccine N=10 |
|----------------------------------------------------|-----------------|--------------------------|--------------|-----------------------------------------|
| Any AE                                             | 11 (84.6%)      | 11 (91.7%)               | 11 (91.7%)   | 9 (90.0%)                               |
| Number of AEs                                      | 58              | 45                       | 54           | 52                                      |
| Number of SAEs                                     | 2               | 0                        | 2            | 1                                       |
| Number of SUSARs                                   | 1               |                          |              |                                         |
| One AE                                             | 1 (7.7%)        | 4 (33.3%)                | 1 (8.3%)     | 1 (10.0%)                               |
| Two AEs                                            | 1 (7.7%)        | 2 (16.7%)                |              |                                         |
| Three or more AEs                                  | 9 (69.2%)       | 5 (41.7%)                | 10 (83.3%)   | 8 (80.0%)                               |
| Any SAE                                            | 2 (15.4%)       |                          | 1 (8.3%)     | 1 (10.0%)                               |
| Any SUSAR                                          | 1 (7.7%)        |                          |              |                                         |
| Any treatment related AE                           | 10 (76.9%)      | 0                        | 0            | 9 (90.0%)                               |
| Any treatment related SAE                          | 2 (15.4%)       |                          |              | 1 (10.0%)                               |
| Any AE leading to study drug discontinuation       | 2 (15.4%)       |                          | 1 (8.3%)     | 4 (40.0%)                               |
| Number of AE leading to study drug discontinuation | 2               |                          | 1            | 7                                       |

**AE by System Organ Class (SOC) and Preferred term (PT) ([no. of events] no of patients (% of patients))**

| System Organ Class                                   | Preferred term                              | etoricoxib N=13 | H56:IC31 TB vaccine N=12 | Control N=12  | etoricoxib and H56:IC31 TB vaccine N=10 |
|------------------------------------------------------|---------------------------------------------|-----------------|--------------------------|---------------|-----------------------------------------|
| Blood and lymphatic system disorders                 | Anaemia                                     |                 |                          | [1] 1 (8.3%)  |                                         |
|                                                      | Leukopenia                                  |                 |                          |               | [1] 1 (10.0%)                           |
|                                                      | Lymphadenopathy                             |                 |                          | [1] 1 (8.3%)  |                                         |
|                                                      | Thrombocytopenia                            |                 |                          |               | [1] 1 (10.0%)                           |
| Gastrointestinal disorders                           | Abdominal discomfort                        | [1] 1 (7.7%)    |                          |               | [1] 1 (10.0%)                           |
|                                                      | Abdominal pain                              | [1] 1 (7.7%)    |                          |               | [2] 2 (20.0%)                           |
|                                                      | Abdominal pain upper                        | [1] 1 (7.7%)    | [1] 1 (8.3%)             | [2] 2 (16.7%) |                                         |
|                                                      | Diarrhoea                                   | [1] 1 (7.7%)    |                          |               |                                         |
|                                                      | Dry mouth                                   | [1] 1 (7.7%)    | [1] 1 (8.3%)             |               |                                         |
|                                                      | Dyspepsia                                   | [1] 1 (7.7%)    | [3] 2 (16.7%)            | [2] 2 (16.7%) |                                         |
|                                                      | Gastritis                                   | [1] 1 (7.7%)    | [1] 1 (8.3%)             |               |                                         |
|                                                      | Haemorrhoids                                | [1] 1 (7.7%)    |                          |               |                                         |
|                                                      | Nausea                                      | [7] 6 (46.2%)   | [4] 4 (33.3%)            | [3] 3 (25.0%) | [6] 5 (50.0%)                           |
|                                                      | Vomiting                                    |                 | [1] 1 (8.3%)             |               | [1] 1 (10.0%)                           |
| General disorders and administration site conditions | Chest pain                                  | [1] 1 (7.7%)    | [3] 3 (25.0%)            |               |                                         |
|                                                      | Disease progression                         | [1] 1 (7.7%)    |                          |               |                                         |
|                                                      | Fatigue                                     | [9] 8 (61.5%)   | [4] 4 (33.3%)            | [6] 6 (50.0%) | [3] 3 (30.0%)                           |
|                                                      | Pyrexia                                     |                 |                          |               | [1] 1 (10.0%)                           |
|                                                      | Vaccination site pain                       |                 |                          |               | [2] 2 (20.0%)                           |
| Immune system disorders                              | Immune reconstitution inflammatory syndrome |                 |                          |               | [1] 1 (10.0%)                           |
| Infections and infestations                          | Lymph node abscess                          |                 |                          |               | [1] 1 (10.0%)                           |
|                                                      | Nasopharyngitis                             | [1] 1 (7.7%)    |                          |               |                                         |
|                                                      | Otitis externa                              |                 |                          | [1] 1 (8.3%)  |                                         |
|                                                      | Respiratory tract infection                 | [1] 1 (7.7%)    |                          |               |                                         |
|                                                      | Tooth infection                             |                 | [1] 1 (8.3%)             |               |                                         |
| Injury, poisoning and procedural complications       | Contusion                                   |                 |                          |               | [1] 1 (10.0%)                           |
| Investigations                                       | Blood creatine phosphokinase increased      |                 | [2] 1 (8.3%)             |               |                                         |
|                                                      | Cardiac murmur                              |                 |                          | [1] 1 (8.3%)  |                                         |
|                                                      | Hepatic enzyme increased                    | [8] 5 (38.5%)   | [3] 3 (25.0%)            | [3] 2 (16.7%) | [4] 3 (30.0%)                           |
|                                                      | Weight decreased                            |                 |                          | [2] 2 (16.7%) |                                         |
| Metabolism and nutrition disorders                   | Decreased appetite                          |                 |                          | [4] 4 (33.3%) | [1] 1 (10.0%)                           |
| Musculoskeletal connective tissue disorders          | Arthralgia                                  | [3] 3 (23.1%)   | [3] 3 (25.0%)            | [6] 6 (50.0%) | [2] 2 (20.0%)                           |
|                                                      | Myalgia                                     | [3] 3 (23.1%)   | [4] 2 (16.7%)            | [2] 2 (16.7%) | [2] 2 (20.0%)                           |

|                                                 |                                 |               |               |               |               |
|-------------------------------------------------|---------------------------------|---------------|---------------|---------------|---------------|
|                                                 | Pain in extremity               |               |               |               | [1] 1 (10.0%) |
| Nervous system disorders                        | Cerebral ischaemia              |               |               | [1] 1 (8.3%)  |               |
|                                                 | Dizziness                       | [3] 3 (23.1%) |               | [1] 1 (8.3%)  | [2] 2 (20.0%) |
|                                                 | Dysgeusia                       | [1] 1 (7.7%)  |               | [1] 1 (8.3%)  | [1] 1 (10.0%) |
|                                                 | Headache                        | [6] 6 (46.2%) | [5] 5 (41.7%) | [2] 2 (16.7%) | [2] 1 (10.0%) |
|                                                 | Muscle contractions involuntary |               |               | [1] 1 (8.3%)  |               |
|                                                 | Paraesthesia                    |               | [1] 1 (8.3%)  |               |               |
|                                                 | Presyncope                      | [1] 1 (7.7%)  |               |               |               |
| Pregnancy, puerperium and perinatal conditions  | Pregnancy                       |               |               | [1] 1 (8.3%)  |               |
| Psychiatric disorders                           | Anxiety                         |               |               |               | [1] 1 (10.0%) |
| Renal and urinary disorders                     | Pollakiuria                     |               |               |               | [1] 1 (10.0%) |
| Reproductive system and breast disorders        | Testicular pain                 |               |               |               | [1] 1 (10.0%) |
| Respiratory, thoracic and mediastinal disorders | Cough                           |               | [1] 1 (8.3%)  | [2] 1 (8.3%)  | [2] 2 (20.0%) |
|                                                 | Dyspnoea                        |               | [1] 1 (8.3%)  |               | [1] 1 (10.0%) |
|                                                 | Haemoptysis                     |               |               | [1] 1 (8.3%)  |               |
| Skin and subcutaneous tissue disorders          | Dermatitis acneiform            |               | [1] 1 (8.3%)  | [1] 1 (8.3%)  |               |
|                                                 | Eczema                          |               |               | [2] 2 (16.7%) |               |
|                                                 | Hand dermatitis                 |               |               |               | [1] 1 (10.0%) |
|                                                 | Hyperhidrosis                   |               | [1] 1 (8.3%)  |               | [1] 1 (10.0%) |
|                                                 | Night sweats                    | [1] 1 (7.7%)  |               | [2] 2 (16.7%) | [1] 1 (10.0%) |
|                                                 | Pruritus                        | [2] 2 (15.4%) | [1] 1 (8.3%)  | [2] 2 (16.7%) | [4] 3 (30.0%) |
|                                                 | Pruritus generalised            |               | [1] 1 (8.3%)  |               |               |
|                                                 | Rash                            | [1] 1 (7.7%)  | [1] 1 (8.3%)  | [3] 3 (25.0%) | [1] 1 (10.0%) |
|                                                 | Rash generalised                |               |               |               | [1] 1 (10.0%) |
|                                                 | Urticaria                       | [1] 1 (7.7%)  |               |               |               |
| Vascular disorders                              | Diastolic hypertension          |               | [1] 1 (8.3%)  |               |               |
|                                                 | Haematoma                       |               |               |               | [1] 1 (10.0%) |

**Severe adverse events by System Organ Class (SOC) and Preferred term (PT ([no. of events] no. of patients (pct of patients) )**

| System Organ Class                                   | Preferred term       | etoricoxib N=13 | H56:IC31 TB vaccine N=12 | Control N=12 | etoricoxib and H56:IC31 TB vaccine N=10 |
|------------------------------------------------------|----------------------|-----------------|--------------------------|--------------|-----------------------------------------|
| Gastrointestinal disorders                           | Abdominal pain       |                 |                          |              | [1] 1 (10.0%)                           |
|                                                      | Abdominal pain upper | [1] 1 (7.7%)    |                          |              |                                         |
| General disorders and administration site conditions | Fatigue              | [1] 1 (7.7%)    |                          | [1] 1 (8.3%) |                                         |
| Nervous system disorders                             | Cerebral ischaemia   |                 |                          | [1] 1 (8.3%) |                                         |
| Skin and subcutaneous tissue disorders               | Rash generalised     |                 |                          |              | [1] 1 (10.0%)                           |

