## Supplementary Table 8. Follow-up time, study discontinuation and adherence

### Follow-up time and study discontinuation all arms - Safety Analysis Set\* (N=47)

|                                                                  | Etoricoxib
(N = 13) | H56:IC31
(N = 12) | Controls
(N = 12) | Etoricoxib +
H56:IC31
(N = 10) |
|------------------------------------------------------------------|------------------------|----------------------|----------------------|--------------------------------------|
| Follow-up time in days                                    |                        |                      |                      |                                      |
| Mean (SD)                                                        | 200.4 (83.0)           | 227.3 (44.4)         | 214.0 (84.1)         | 199.8 (93.6)                         |
| Min, Max                                                         | 11.0, 265.0            | 88.0, 250.0          | 50.0, 330.0          | 20.0, 285.0                          |
| Did the subject complete the study                        |                        |                      |                      |                                      |
| Yes                                                              | 9 (69%)                | 10 (83%)             | 9 (75%)              | 6 (60%)                              |
| No                                                               | 4 (31%)                | 2 (17%)              | 3 (25%)              | 4 (40%)                              |
| Reasons for study discontinuation                         |                        |                      |                      |                                      |
| Voluntary discontinuation by the subject                         | 0 (0%)                 | 1 (50%)              | 0 (0%)               | 0 (0%)                               |
| Safety reason as judged by the Principal Investigator            | 1 (25%)                | 0 (0%)               | 0 (0%)               | 2 (50%)                              |
| Major protocol deviation                                         | 1 (25%)                | 0 (0%)               | 0 (0%)               | 0 (0%)                               |
| Pregnancy during follow-up                                       | 0 (0%)                 | 0 (0%)               | 2 (67%)              | 1 (25%)                              |

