### Adverse events by SOC and PT([no. of events] no of patients (% of patients))

| System Organ Class                                   | Preferred term              | etoricoxib N=11 | H56:IC31 TB vaccine N=11 | Control N=10  | etoricoxib and H56:IC31 TB vaccine N=8 |
|------------------------------------------------------|-----------------------------|-----------------|--------------------------|---------------|----------------------------------------|
| Blood and lymphatic system disorders                 | Anaemia                     |                 | [1] 1 (9·1%)             |               |                                        |
|                                                      | Lymphadenopathy             |                 | [1] 1 (9·1%)             |               |                                        |
| Gastrointestinal disorders                           | Abdominal pain              | [1] 1 (9·1%)    | [1] 1 (9·1%)             | [1] 1 (10·0%) | [1] 1 (12·5%)                          |
|                                                      | Diarrhoea                   |                 |                          | [1] 1 (10·0%) |                                        |
|                                                      | Lip ulceration              |                 |                          |               | [1] 1 (12·5%)                          |
|                                                      | Nausea                      | [1] 1 (9·1%)    | [1] 1 (9·1%)             | [2] 1 (10·0%) | [1] 1 (12·5%)                          |
|                                                      | Toothache                   |                 | [1] 1 (9·1%)             |               |                                        |
|                                                      | Vomiting                    |                 |                          | [1] 1 (10·0%) |                                        |
| General disorders and administration site conditions | Chest pain                  | [1] 1 (9·1%)    |                          |               |                                        |
|                                                      | Fatigue                     | [2] 2 (18·2%)   | [3] 3 (27·3%)            |               | [1] 1 (12·5%)                          |

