## **6.3 Criteria for Patient Discontinuation**

### **6.3.1 Rules for Discontinuing the whole Study in an Individual Subject**

Patients may be discontinued from study treatment and assessments at any time. Patient is also at any time free to discontinue his/her participation in the study, without any further explanation or prejudice to further treatment.

Specific reasons for discontinuing a patient for this study are:

- Safety reason as judged by the Principal Investigator
- Major protocol deviation
- Incorrect enrolment ie, the patient does not meet the required inclusion/exclusion criteria for the study
- Patient's non-compliance to study treatment and/or procedures
- Patient lost to follow-up
- A female patient becoming pregnant
- TB disease progression
- Development of autoimmune disease or immunosuppression
- Death
- Other

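### Three discontinuations for pregnancy are recorded but only one pregnancy is counted as an adverse event, so the primary safety outcome treats the same event in two ways

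*Protocol*

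**What the plan says.** Supplementary Table 8 has a row "Pregnancy during follow-up" among the reasons for study discontinuation. On the safety analysis set (N=47) it reads 0 for etoricoxib, 0 for H56:IC31, 2 for controls and 1 for etoricoxib + H56:IC31. On the full analysis set (FAS, N=40) it reads 1 for controls and 1 for etoricoxib + H56:IC31.

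Supplementary Table 9 (day 0 to 84) has a system organ class row "Pregnancy, puerperium and perinatal conditions" with the preferred term Pregnancy: one event in one control (8.3%) and nothing in the other arms. Supplementary Tables 10 (day 85 to 154) and 11 (day 155 to 238) have no pregnancy row in any arm. The sub-tables of Tables 9 to 11 for severe events, serious events, SUSARs and events leading to drug discontinuation have none either.

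Section 6.3.1 lists "A female patient becoming pregnant" among the reasons for discontinuing a subject. Section 8.1.1 defines an AE in general terms and does not mention pregnancy, and no other part of section 8 says whether a pregnancy is recorded as one. Section 8.4 sets AE collection from day 0 to day 238. The detailed statistical methods make the occurrence of AEs by arm and interval the primary outcome, described without formal testing.

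**The concern.** The same kind of event is an AE in one patient and not in two others. AE occurrence by arm is the primary outcome, so coding should not differ between patients or arms without a stated reason. From Tables 9 to 11 alone, pregnancy appears once and only in the control arm. With Table 8 alongside, there are two in controls and one in the combination arm. The case missing from the AE tables in the combination arm is the only one in a patient allocated to investigational product.

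**Working it through.** **1. Count the pregnancies.**

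| Source | Etoricoxib | H56:IC31 | Controls | Etoricoxib + H56:IC31 | Total |
|---|---|---|---|---|---|
| Table 8, safety set | 0 | 0 | 2 | 1 | 3 |
| Table 8, FAS | 0 | 0 | 1 | 1 | 2 |
| Table 9, day 0 to 84 | 0 | 0 | 1 | 0 | 1 |
| Table 10, day 85 to 154 | 0 | 0 | 0 | 0 | 0 |
| Table 11, day 155 to 238 | 0 | 0 | 0 | 0 | 0 |

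The gap is 3 − 1 = 2: one control and the combination-arm patient.

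**2. Check that no row was lost.** The bracketed event counts by preferred term were added and compared with the number of AEs in each summary.

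- Controls: 54, 15 and 7 in Tables 9, 10 and 11; stated 54, 15 and 7.
- Etoricoxib + H56:IC31: 52, 15 and 8; stated 52, 15 and 8.

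All six sums agree, and the 54 includes the one listed pregnancy. The other two were neither dropped from a listing nor counted without being listed.

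**3. Ask whether timing explains the gap.** Follow-up lengths in Table 8 give a partial answer.

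- The two controls outside the FAS have 12 × 214.0 − 10 × 246.7 = 2568 − 2467 = 101 days of follow-up between them. The minimum in the arm is 50 days, so each had about 50. One of them left for pregnancy (2 in the safety set less 1 in the FAS). That fits the single pregnancy listed in day 0 to 84.
- The FAS control who left for pregnancy had at least 168 days, the FAS minimum for controls. This is most likely the unlisted control event.
- The combination-arm patient is in the FAS, where the minimum is 180 days. Table 11 has N=8 for this arm, equal to the FAS count of 8, so the patient is apparently in its denominator.

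The combination-arm and FAS control patients were thus followed for at least 180 and 168 days, within an AE collection period that runs to day 238.

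**4. Size under each uniform rule.**

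- Pregnancy is not an AE: Table 9 controls go from 54 to 53 events. One control in Table 9 had exactly one AE. If that AE was the pregnancy, any AE falls from 11/12 to 10/12; otherwise it stays at 11/12.
- Pregnancy is an AE: the tables would show 2 in controls and 1 in the combination arm, instead of 1 and 0.
  - Combination arm, probably Table 11: 8 to 9 events, any AE 3/8 (37.5%) to at most 4/8 (50%).
  - Control in Table 10: 15 to 16 events, any AE 5/10 (50%) to at most 6/10 (60%).
  - Control in Table 11: 7 to 8 events, but no proportion can be given. The denominator of 9 equals the 9 controls who completed the study, and the pregnant FAS control is the arm's one FAS non-completer.

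The proportions are upper limits because the patient may already be counted for another AE.

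**The case against.** Four points can be made on the other side.

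- **The cases are not hidden.** A reader might infer that the combination-arm pregnancy is missing from the safety results altogether. It is not: Table 8, on the safety analysis set, shows it by arm. Only the AE tables lack it. This stands.
- **Exposure is not shown.** A reader might infer that this was a pregnancy exposed to the investigational products. Table 8 shows that all 8 FAS patients in the arm received both vaccinations and at least 80% of their tablets. But etoricoxib ends and the second vaccination is given at day 140, section 6.2.2 calls for a urine pregnancy test immediately before each immunisation, and no conception or detection date is given. Exposure is possible and undetermined. This stands.
- **No rule makes pregnancy an AE.** Leaving a pregnancy in the discontinuation table alone is compatible with section 8.1.1, and the AE sums are right. So a required AE has not been shown to be missing. This stands, but it does not explain why one control pregnancy was coded as an AE.
- **The interval of the control event is uncertain.** A reader might move Table 11 controls from 4/9 to 5/9. That would put in the numerator a patient who is apparently not among the 9. Follow-up length also does not date a pregnancy: a control with at least 168 days would be expected in the day 155 to 238 set, yet seems not to be there. This stands.

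The consequence is also limited, because safety is descriptive and no between-arm test depends on these counts.

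**Conclusion.** The inconsistency is real and minor. Three patients discontinued for pregnancy, one pregnancy is coded as an AE, and the other two, one control and the only one allocated to investigational product, are in Table 8 but in no AE table. Whichever uniform rule is chosen, at least one published AE count changes: one event fewer in Table 9 controls, or two more events across the later tables.

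The 3-against-1 count is a direct reading and rests on no assumption. The placing of the two unlisted events does: it takes follow-up length as a rough guide to timing, which is reasonable for the combination arm and doubtful for the control. The documents do not support reading this as an omitted mandatory AE, as a demonstrated exposure during pregnancy, or as a pregnancy concealed from the safety reporting.

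**What to change.** State one rule for pregnancies, apply it to all arms, and reconcile Table 8 with Tables 9 to 11. Two versions would work.

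- Take pregnancy out of the AE counts, restate Table 9 controls as 53 events, and list all three pregnancies separately by arm, with timing relative to investigational product and outcome.
- Code all three as AEs, each in the interval of its actual onset date, and restate the affected tables. If the control event falls in day 155 to 238, check the Table 11 control denominator of 9 before giving a proportion.

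The first is simpler and also answers the exposure question that the tables leave open. The cost is one or two recoded records and one small listing.
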